## Discussion

Evidence so far suggests that strengthening exercises offers significant improvements in pain and function [24, 58], but is not associated with reductions in depression [59]; thus, education for pain coping and cognitive behavioral skills improves psychological functioning in KOA patients [22, 59–64]. This study aims not only to investigate the benefits of blended web-based rehabilitation (exercise and coping education skills implemented in a self-managed manner with minimal supervision) and enhanced with outdoor PA, but also whether these potential benefits can help patients change their level of PA, behavior and perceptions related to KOA, and therefore their routine daily life.

### Strengths and limitations

The study design has several strengths. First, considerable attention has been paid to quality control with the contribution of the established award-winning program ESCAPE-knee pain. Online ESCAPE-knee pain has been found to improve functioning, understanding, and confidence by combining education, advice, and simple coping strategies with functional exercise material [25, 26]. The program does not require specialized training, sophisticated exercises, or equipment for the participants, so it could be implemented and replicated easily. Second, the outcome measures selected are valid, responsive and reliable, cover a range of clinically important concepts, and include those recommended for clinical trials of OA [62]. Third, a well-designed web-based intervention in which patients’ can report their experiences with home exercises via phone calls, provide physiotherapists information about patients’ individual needs for guidance. Research in web-based interventions has focused on interventions without human physical support. Unfortunately, the effects of these interventions have been shown minimal, especially in the long-term [65, 66]. These minimal effects may be partly explained by the absence of face-to-face guidance [67]. Therefore, the combination of web-based intervention with face-to face minimal supervision as well as the inclusion of real life outdoor activity is more promising [65]. The study has been designed with attention to methodological quality characteristics such as randomization, concealed allocation and blinded outcome assessment. Finally, the novelty of the study is that the blended program will be provided in weak structured areas where cost-effective options of physiotherapy care are mostly needed.

Limitation of the study is the unblinded nature of the physiotherapist delivering intervention and guidance. In the case of accessibility limitations during the assessment sessions due to the restrictions imposed by COVID-19 measures will be dealt with telecommunication. Moreover, the level of PA will not be measured objectively prior to the beginning of exercise program.

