#### Blended web-based and outdoor PA program (WB-OPA)

Participants randomized to blended web-based rehabilitation (based on ESCAPE-knee pain online resources) will participate in an exercise-based rehabilitation program designed to improve physical function by integrating exercise, PA, education on the condition, and self-management strategies. ESCAPE-pain stands for Enabling Self-management and Coping with Arthritic Pain using Exercise. It is an evidence-based, cost effective, rehabilitation program for people with chronic OA that combines a progressive exercise program with simple advice strategies on how to self-manage their condition [25, 26]. ESCAPE-pain delivers the NICE core recommendations of exercise and education for the management of OA. The physiotherapist teaching the exercise program to participants has undertaken the accredited ESCAPE-pain course. The blended character of the rehabilitation is based on two components: a) physical exercise delivered via web-based video and outdoor PA, and b) education management strategies delivered again via web-based video. In the introductory face-to face session, individual passwords will be provided to this group in order to register and have access to the rehabilitation program. Participants will be instructed to attend 12 exercise sessions, for 6 weeks, twice weekly. More specifically, participants will perform a 35–40 minutes simple exercise regimen based on pre-recorded video that will progress as they improve. The exercises train elements of joint flexibility, muscle strength, balance, and muscle endurance. Additionally, each week, participants will be encouraged to attend a 5–10 minutes pre-recorded advisory video session by the physiotherapist. The advisory sessions include information on OA related topics, i.e. risk factors, clinical manifestations, feasible strategies like ice, dietary control, pacing, goal setting, and overcoming psychological distress. Table 1 presents the study schedule.

**Table 1 pone.0268652.t001:** Description of the study schedule.

Baseline	• Eligibility criteria assessed by investigator
	• Read patient information letter
	• Sign informed consent
	• Completing baseline assessment measurement
	• Schedule face- to face appointment for week 1
Introductory face-to -face session	• Provision of information on OA, benefits of PA on pain by PT
week 1	• Familiarization patient with webpage environment

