	• Registration patient and provide digital codes for entrance in the exercise and education video-material
	• Instruction of exercises of week 1 in the home environment
	• Selection and agreement on outdoor journey route, provide relevant map
	• Instruction of the use of pedometer
	• Instruction of the use/ completion of diary weekly log
	• Determination of goals
	• Video-education session 1
	• Two video home-exercise sessions
	• Schedule phone call for week 2
Week 2- week 5	• Video-education session 2–5
	• Two video home-exercise sessions
	• Completion of log-book
	• Discussion of progress by phone call supervision with PT
	• Schedule phone call for following weeks
	• Schedule appointment for follow-up session of week 6
Week 6	• Video-education session 6
	• Two video home-exercise sessions of week 6
	• Completion of log-book
	• Follow-up assessment measurement week 6 by investigator
	• Face-to-face session with PT to monitor progress, logbook and goals on exercise and outdoor activity, discuss increase of selected outdoor PA
	• Encouragement of continuing exercise and PA
	• Encouragement to ask phone call supervision (at their own will)
	• Schedule a follow-up assessment of week 12
Week 7–11	• Self-selected home exercise
	• Selected outdoor activity (walking route)
	• Schedule appointment for week 12
Week 12	• Final follow up assessment by investigator
	• Face-to-face session with PT to discuss long-term goal and support for maintaining active lifestyle.

In addition to the web-based exercise program, the experimental group will be prescribed to perform thrice weekly a pre-determined walk of 500-800m (a walking dose of 70 minutes per week in separate sessions of at least 10 minutes duration), according to their individual potential. The journey routes selected, based on the distance, safety, comfort and enjoyable paths (i.e. local green parks, pedestrian shopping malls, sports courts) with a relevant map will be provided (with analytic description, photos of key corners, benches for rest etc.). Walking programs are known to have beneficial effects on knee pain and function for people with mild to moderate KOA [27, 31–36].

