#### Adherence strategies

To increase the likelihood of adherence to the interventions, the following behavioural change techniques and strategies will be used. First, each participant will have a planning session with a physiotherapist of up to 30 min to plan the location, day and time of day for each walk, and reinforce that each walk was moderate intensity in at least a 10 min. Second, regular physiotherapy supervision and monitoring each week with regular phone calls based on patient preference will be offered. If any complication or query should arise, participants could discuss it in the weekly phone calls or contact directly the physiotherapist, and they will be informed of the procedure to follow. Third, each participant will wear a pedometer and record the number of steps taken and time spent walking during each session in a logbook. All participants will complete the daily logbook to record the time (in minutes) spent in activity either walking or exercising in for each walking session over the 12 weeks (Table 2). The physiotherapist will monitor the participant’s logbook at each weekly supervisory session (by phone). Fourth, participants will be encouraged to engage social supports such as walking with a friend, family member if they chose to. They will also describe any changes to their usual care of their KOA and any problems with their knee while doing their walking program each week.

**Table 2 pone.0268652.t002:** Logbook diary to monitor compliance, duration and frequency of exercise and outdoor walking activity weekly.

	Week 1		Week 2		Week 3		Week 4…	..Week 10	Week 11	Week 12
	Exercise (-/min)	Walking (-/min/step)	Exercise (-/min)	Walking (-/min/steps)	Exercise (-/min)	Walking (-/min/steps)	Exercise (-/min)	…	…	Walking (-/min/steps)
Monday										
Tuesday										
Wednesday										
Thursday										
Friday										
Saturday										
Sunday										

Participants in both groups will be free to withdraw from the study at any time, but the withdrawal rates and reasons will be recorded.

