#### Secondary outcome measures

c)Physical Function:
The 30-second Chair Stand test (30 CTS) provides a direct, objective measure (number/times participants can rise to a full standing position from sitting and return to sitting, with arms crossed and held against the chest, in 30 seconds will be counted). The 30 CTS has been recommended within the minimal core set of performance-based outcome measures in OA research and clinical practice [38, 43].The timed up and go (TUG) test evaluates walking speed and mobility and has been found as valid and reliable in KOA patients [43, 44]. Participants are instructed to stand up from a standard height chair and walk at their normal pace around a marker 3 meters away before returning to the chair and sitting down again. TUG has been found as valid and reliable in KOA patients [45].d)PA level:Habitual PA will be measured in three ways, 1) using a questionnaire, 2) second using a scale and 3) using a pedometer.
The Modified Baecke Physical Activity Questionnaire (mBQ), validated in samples adults ≥ 55 years of age [46, 47], to assess PA.The UCLA scale indicates patients’ most appropriate activity level, with 1 defined as “no PA, dependent on others” and 10 defined as “regular participation in impact sports”, and has been found as the only scale discriminating between insufficiently and sufficiently active patients in KOA [48].A pedometer (Yamax SW200 digi-walker) has been compared with actual steps in multiple studies [49–54] and consistently performs well. This pedometer will be clipped to the participants’ waistband on either the left or right hip, each morning and will be removed it at bedtime for 3 consecutive days [54] on three occasions (baseline, week 6 and week 12) to record the number of steps taken per day.e)Health-related QoL: This will be assessed using the Short-Form-12 QoL instrument which is widely used measure of general health and QoL status [55].f)Psychological Function: Tampa Scale for Kinesiophobia (TSK). The TSK will be examined to provide a brief fear of movement scale that is valid and reliable in people with OA [56, 57].

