#### Randomisation- Allocation concealment

Recruited participants will be randomly allocated to either the experimental group or control group at a 1:1 ratio. Random numbers will be generated using a computer software program run by an external statistician. After baseline assessment, participants will be provided an envelope according to the randomization sequence by a volunteer undergraduate who will prepare consecutively numbered, sealed, opaque envelopes. The envelopes will be kept in a locked location accessible only by the unblinded physiotherapist (MM). The physiotherapist will then schedule the participants’ first appointment.

The investigator (AK) performing all assessments will be blinded to the participant randomization assignment and will not be involved in providing the interventions. Participants will be requested not to disclose details about their treatment to the outcome investigator. The statistician will be blind to group allocation until completion of the statistical analyses.

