#### Statistical analysis

We will calculate the proportion of enrolled participants out of all eligible patients, the adherence rate and the dropout rates. The Shapiro-Wilk Test will be used to determine the normality of the data. Descriptive statistics will be presented for each group as mean change (standard deviation (SD), 95% confidence intervals) for all outcomes from baseline to 12 weeks. Analysis of covariance (ANCOVA) will be performed using IBM SPSS version 24 for all the primary and secondary outcome measures with baseline measures as covariates. In the case of missing data in the relevant directions according on how to handle missing data in every outcome measure will be followed.

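### The protocol contradicts itself on whether a step count is taken before the programme, which leaves the baseline-adjusted analysis of steps unsettled

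*Protocol article*

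**What the plan says.** Five places in the protocol article bear on the step count.

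- **Secondary outcome measures.** Habitual physical activity is measured by the modified Baecke questionnaire, the UCLA scale and a pedometer. The pedometer is worn for three consecutive days "on three occasions (baseline, week 6 and week 12) to record the number of steps taken per day".
- **Strengths and limitations.** Among the limitations, the article states that "the level of PA will not be measured objectively prior to the beginning of exercise program".
- **Table 1 (study schedule).** The Baseline row has the general entry "Completing baseline assessment measurement" and names no instruments. The line "Instruction of the use of pedometer" appears only under the week-1 introductory session, together with route selection, the weekly log and the first home-exercise videos.
- **Randomisation and allocation concealment.** "After baseline assessment, participants will be provided an envelope according to the randomization sequence". Then: "The physiotherapist will then schedule the participants’ first appointment". The week-1 session therefore comes after allocation.
- **Statistical analysis.** All primary and secondary outcomes are analysed by ANCOVA "with baseline measures as covariates", and mean change from baseline to 12 weeks is described for all outcomes.

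Adherence strategies gives the pedometer a second use: "each participant will wear a pedometer and record the number of steps taken and time spent walking during each session in a logbook".

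**The concern.** The stated analysis of steps needs a baseline value that one section promises and another denies. The schedule does not settle which is right, because the only pedometer instruction it names falls after allocation.

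Steps are the only objective evidence on physical activity, which is the subject of Hypothesis 1 and part of Hypothesis 3. If site staff follow the limitation sentence, there is no covariate and no change score. If they follow Table 1 and take the first reading once the pedometer has been explained in week 1, the covariate is collected after allocation, when the two arms already have different instructions. Neither can be repaired once a participant has been allocated.

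**Working it through.** **1. Do the two statements conflict?** Of the three activity measures, two are self-reported and one, the pedometer, is objective. A baseline pedometer reading taken before the programme is an objective measurement before the programme. The outcome section plans one and the limitation says there is none. Both can be true only if baseline means a time after the programme has begun.

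**2. What readings does the text allow?**

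| Reading | Support in the article | Consequence for steps |
|---|---|---|
| A. Worn before allocation | Outcome section names baseline as an occasion; envelopes follow baseline assessment | Planned ANCOVA and change scores are sound; the limitation sentence is wrong |
| B. No baseline reading | Limitation sentence | ANCOVA on baseline and change from baseline cannot be computed |
| C. Worn after the week-1 session | Pedometer instruction listed only in week 1 | Covariate is measured after allocation |

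**3. Size under reading B.** The article gives no figures for steps, so the baseline-to-follow-up correlation r is an assumption. ANCOVA multiplies the residual variance by 1 − r², so the reduction is r²:

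- r = 0.6: 0.6² = 0.36, a 36% reduction.
- r = 0.7: 0.7² = 0.49, a 49% reduction.

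Without a baseline, all of this reduction is lost. As an illustration in terms of power, take 22 per arm and an effect on steps just large enough for ANCOVA to have 80% power at two-sided 5%. The standardised signal under ANCOVA is then 1.960 + 0.842 = 2.802. Without the covariate it shrinks by the factor √(1 − r²), and power is Φ(2.802 × √(1 − r²) − 1.960):

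- r = 0.6: 2.802 × 0.800 − 1.960 = 0.28, power about 61%.
- r = 0.7: 2.802 × 0.714 − 1.960 = 0.04, power about 52%.
- Wider range: about 76% at r = 0.3 and 39% at r = 0.8.

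The trial is not powered on steps, so these figures show scale only.

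**4. Direction under reading C.** The adjusted contrast is the follow-up difference minus the slope times the difference in the covariate. Randomisation makes that second difference zero on average only if the covariate precedes allocation. From week 1 the web-based arm is prescribed three walks a week plus two video exercise sessions, and the control arm five walks a week. If controls record more steps in that week and the slope is positive, adjustment moves the contrast toward the web-based arm. If the video sessions add steps, or total walking is the same in both arms, it moves less or the other way. The article gives the web-based arm both a distance per walk (500 to 800 m) and a weekly walking time (70 minutes), and gives controls the same parameters apart from frequency. It therefore does not determine which arm would record more steps. No size is put on this bias.

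**5. What is untouched.** The recruitment total rests on KOOS and reproduces: 22 / 0.8 = 27.5, rounded up to 28 per arm, 56 in all. It does not depend on the step count.

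**The case against.** The strongest reply is that reading A is available and natural. The outcome section names baseline as a pedometer occasion, and envelopes are given only after baseline assessment, so together they describe a step count taken before allocation. The Baseline row of Table 1 itemises no instruments, so the pedometer's absence there proves nothing. The week-1 pedometer instruction sits next to the logbook instruction and may serve the session-by-session recording described under Adherence strategies. Fig 1, the assessment schedule, is not shown in the text available.

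All of this stands. A reader might infer that the step analysis has no valid baseline whichever way the text is read. The document does not support that, because a reading taken before allocation is compatible with everything except the limitation sentence. Nor does it say that a baseline reading would include prescribed walking: Table 1 gives no order of days within week 1. A reader might also infer that adjusting for a week-1 count would necessarily dilute the treatment effect, but the direction is open.

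The reply does not remove the contradiction. The limitation sentence is not a detail left to a fuller document. It states the opposite of the outcome section.

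It is also fair to say that the reach is limited. Steps are one of three measures in one secondary domain, and the Baecke questionnaire and the UCLA scale also address Hypotheses 1 and 3.

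**Conclusion.** The article contradicts itself on whether a pre-programme step count exists, and the schedule does not resolve it. That much is certain from the text. The consequences are conditional:

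- **If the limitation sentence is right**, ANCOVA and change from baseline cannot be computed for steps. The unadjusted follow-up comparison remains unbiased by randomisation but is less precise. The 36 to 49% figure rests on an assumed correlation of 0.6 to 0.7.
- **If the reading is taken after the week-1 session**, adjustment uses a covariate that allocation may already have affected. The contrast can be biased by an amount and in a direction that the document does not fix.
- **If the reading is taken before allocation**, the analysis is sound and only the wording is wrong.

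The scope is one secondary measure, relevant to Hypotheses 1 and 3. KOOS, the pain rating scale, the Baecke questionnaire, the UCLA scale and the sample size are unaffected. The point deserves correction because a covariate collected too late cannot be recovered.

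**What to change.** Reconcile Secondary outcome measures, Table 1, Randomisation and Strengths and limitations, in one of two ways.

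**Preferred.** State that the pedometer is issued and explained at the baseline visit, and that the three-day reading is completed and recorded before the envelope is opened. Add this to the Baseline row of Table 1. Any week-1 instruction for the logbook can stay, labelled as such. Correct the limitation sentence to match.

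**If no step count can be taken before allocation.** Keep the limitation, remove baseline from the pedometer occasions under Secondary outcome measures, and state under Statistical analysis that steps are compared at follow-up without baseline adjustment and without change scores.

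**Cost.** The preferred option needs no new device. Allocation waits a few days, and the reading has to be returned before the envelope is opened, a step that the article does not yet describe. The alternative costs only wording, but gives up the precision shown above.

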## Abbreviations

KOA: knee osteoarthritis
KOOS: Knee Injury Osteoarthritis Outcome Score
Mbq: Modified Baecke questionnaire
MCID: minimal important clinical difference
PA: physical activity
QoL: quality of life
SF-12: short form 12
TSK: Tampa scale for Kinesiophobia
VAS: visual analogue scale
WB-OPA: web based outdoor physical activity
